#### Objective Psychophysiology Data Analyses

To accurately identify peaks and not simply gradual increases in skin conductance observed over time, we will filter skin conductance data with a threshold value of 0.04 µS and average over 5 seconds [81,82]. As our study involves movement in a VR space in addition to exposure to a potential stress-inducing situation, we will filter the data with a lower limit of 40 bpm and an upper limit of 200 bpm [83]. Heart rate will also be averaged over 5 seconds. Following averaging, we will use open-source filters for preprocessing the data; then, the psychophysiological data will be processed with existing packages in MATLAB and Python. To correlate the DERS-16 and secondary outcome measures (CORE, WEMWBS, GAD-7, PHQ-9, and PC-PTSD-5) with psychophysiological data, we will employ nonparametric regression analyses in R Statistical and Computing Software. In addition, we will explore preliminary cutoff sum scores for therapeutic response by plotting receiver operating characteristic curves and conducting AUC analyses. We will also compare baseline to postintervention (second baseline) changes in psychophysiology using regression models. Cohen *d* or nonparametric tests will calculate the effect size between groups A and B.

### Ethical Approval

The protocol was approved by the Research Ethics Board of the Centre Integré de Santé et Services Sociaux de l’Ouest de l’Ile (IUSMD 21-52), and it follows the standards of the World Health Organization’s Helsinki Declaration 1975, revised in 2013. Approval for the protocol was granted by the Douglas Mental Health University Institute Ethics Review Board (IUSMD 21-52). In accordance with Tri-Council Policy Statement 2 and guidelines by the Inuit Tapiriit Kanatami and Nunavut Research Institute, the consent process involves both community and individual consent [84,85]. First, we consulted Inuit representational organizations and co-designed with community members. Before participation, we will obtain written, informed consent from all participants, their parent or guardian, or oral consent. Data will be collected and stored with REDCap data collection software, protecting the confidentiality of patients with research IDs. All publications resulting from the research will maintain confidentiality requirements by deidentifying any data. Participants will receive a small financial compensation (gift card) for each hour of in-person participation and surveys (approximately CAD $15 [US $11] per hour).

### Data Dissemination Plan

#### Respect for Inuit Ethical Standards

This research recognizes community protocols and the holistic approach to health and wellness in many Indigenous cultures. By doing that, we respect the ethics framework in Indigenous contexts, composed of principles of respect for persons and concern for Equity and Reciprocity [84]. We seek to follow and respect the principles outlined by Inuit communities in the Tri-Council Policy Statement 2 and the National Inuit Strategy on Research and the Negotiating Research Relationships with Inuit Communities guide [85,86]. These guidelines can apply to Inuit, First Nations, and Métis communities and provide structure for privacy, intellectual property, data custody, and secondary use of data. In adherence to these values, respect for people is necessary, and this is achieved through free, informed, and continued consent of the Inuit community and individual research participants [87]. We also aim toward, “research that is efficacious, impactful, and meaningful to Inuit” [85] in aligning with Inuit research priorities through consultation with representational organizations and the formation of an advisory committee. We strive to bolster social equity through the creation of materials that will belong to the Inuit community.

#### Maximized Participation of the Inuit Community

All results of this research will be validated by the community members and representational organizations and returned to them. We will communicate the final results and a report of the study to all those who participated in it and to the community organizations that would be interested. All publications resulting from the research will maintain the requirements of confidentiality and where they approve, will mention the contribution of everyone involved. The rights of coauthors of Indigenous contributors will be recognized. In any publication derived from this project, participants’ geographical localization will be mentioned as well as the Indigenous group they belong to (Inuit in Québec). This identification of participants as a group will be disclosed but not their personal information.

#### Inuit Ownership of VR Manual and Environments

The rights and permissions to use the treatment manual and VR environments belong to the Inuit community, although they are attached and available in this document. As the main intention of all products of this study is to benefit the Inuit community in Québec, the materials will not be commercialized; however, authors should be consulted before use (to be approved by the Inuit community). Any use of study materials should acknowledge the role of the advisory committee (Inuit community) in developing them and should only be used with express permission (contact SB to initiate this process).

## Results

As this is the prospective registration of an RCT protocol, we do not yet report any results from the trial. This study has been registered prospectively and is available on the web [88] (registration number ISRCTN21831510). Funding was confirmed in January 2020, recruitment is expected to start in March 2023, and is set to finish in August 2025. Expected results to be published in spring 2026.

Any major changes to the protocol will be submitted and approved by our research ethics board, documented on the trial registration platform, and justified in future publication.

## Discussion

### Summary of Objectives

This proof-of-concept study is necessary to respond to the following main concerns: (1) the limited availability of culturally acceptable versions of otherwise validated treatments [89], (2) limited number of RCTs on culturally adapted psychotherapies in Canada, and 3) the use of self-management as an active comparator. This protocol, which compares VR-CBT and Calm Place as self-management, responds to the community’s desire for culturally safe and efficient therapeutic treatments and scientific needs for further investigation into the need and efficacy of culturally adapted treatments. The Inuit community in Montreal co-designed this project with the research team based on their desire for a resilience-based mental health resource.

### Gaps in Research on Culturally Adapted Interventions

Previous evidence of increased acceptability and increased adherence of culturally adapted treatments, with a comparable efficacy to conventional psychotherapy and pharmacological interventions, is promising [90-92]. A recent systematic review of 14 studies conducted in Canada involving culturally adapted mental health treatments concluded that most interventions reduced anxiety, depression, and suicidality among First Nations, Métis, and Inuit [93]. Nevertheless, none of the 14 studies included an RCT, with most RCT evidence for culturally adapted interventions so far being conducted in the United States, low-and middle-income countries, or among refugee populations [90-93]. Furthermore, previous reports have mainly focused on clinic-based treatments or inactive controls. Although our study is randomized, we do ask about preferences between the active treatment and active control treatment and will record the number of participants excluded after accepting only one of the treatments. This will give some indication of the initial perceptions of the acceptability of the treatments.

### Implications of VR With Culturally Adapted Therapies

As technology-assisted psychotherapies advance, VR-CBT or self-management with VR may become complementary options for Indigenous health. In addition to the possibilities of remote treatment (or telemedicine), VR-CBT combines a transdiagnostic and effective treatment modality with potentially improved control and immersion into therapy [1,7]. For instance, therapists can track real-time psychophysiological responses to therapeutic challenges through biofeedback [13]. The client can participate in the therapy in any environment judged most appropriate by the therapist and client to enhance access to treatment. Lastly, Inuit in Nunavik—the northern part of Québec—often experience inconvenience and financial and emotional devastation when attempting to seek care for a health concern, as they may have to travel away from their family to the southern part of the province [94]. We explore several health technologies in the RCT, and future work includes continuing remote therapy.

### Strengths and Limitations

The process of cultural adaptation of psychotherapy was conducted to increase acceptance. The advisory committee recommended study inclusion based on sociocultural background, not trauma symptoms, to improve the cultural safety of the trial. Accordingly, inclusion is based on subjective motivation for improved mental health rather than any categorical diagnosis or subjective or objective need for treatment. In addition, the content of the psychotherapy was modified to confirm safety, according to the comments from the advisory committee. These modifications include reducing exposure and distress-producing exercises and removing the homework normally part of the therapy. A limitation is that these changes may challenge the odds of a psychotherapeutic response.

In our study protocol, we included an active control group, noting the vulnerability of the study population; this may lead to reduced between-group effects. However, only the active treatment is culturally adapted and guided by a psychotherapist, which could improve attendance and thus long-term efficacy in the active treatment group. We will observe the impact of the setting as compared with the content on acceptance while asking for the preference for therapist-guided or self-management treatment. This proof-of-concept RCT will inform us about the potential challenges or limitations of the study protocol, and we can characterize the best outcome measures and calculate power for the further efficacy trial. We consider the scientific risks acceptable, given the extreme imbalance between the need and availability for access to valid and safe treatments.

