**Objective:**

We describe a protocol for a proof-of-concept 2-arm randomized controlled trial (RCT) with Inuit (n=40) in Québec. The primary aims of this research are to investigate the feasibility, benefits, and challenges of the culturally adapted VR-CBT intervention versus an established VR self-management that is available commercially. We will also investigate self-rated mental well-being and objective psychophysiological measures. Finally, we will use proof-of-concept data to identify suitable primary outcome measures, conduct power calculations in a larger trial for efficacy, and collect information about preferences for on-site or at-home treatment.

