## Methods

### Design

The study design is a 2-arm proof-of-concept RCT co-designed with an Inuit advisory committee. The first treatment arm (A) is a 10-week VR-CBT. An active control treatment with minimal attention; the second treatment arm (B) will be using Calm Place as a 10-week self-management. There will be no crossover between conditions, and we will use a 1:1 ratio randomization procedure. The protocol is described in accordance with the SPIRIT (Standard Protocol Items: Recommendations for Interventional Trials) guidelines for interventional trials and is detailed in Multimedia Appendix 1. Ultimately, the goal of the study is to establish the initial feasibility of the VR-CBT and the technologies used and to identify the best measures for initial efficacy.

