#### Randomization and Masking

After receiving informed consent for participation, a research assistant will use a computerized randomization generator to randomly assign participants in a simple 1:1 ratio (VR-CBT or Calm Place). Before randomization, we will show participants the treatment rationales, explaining the 2 possible study groups. They will report their preference for either treatment in a forced-choice question, rate their preference for each treatment on a scale from 1 to 10, and provide comments on why they selected this choice. This information is collected to inform future larger trials and clinical services. The treatment cannot be supplied blinded to the content. However, as the measurements are self-reports and objective measurements, we do not use blinded outcome evaluation. Once random assignments are decided, they will be kept hidden from researchers and research assistants until the participants begin the trial.

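### The article sets setting against content as drivers of acceptance, but both change together with arm, and the structured preference items compare only the two whole packages

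*Protocol article*

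**What the plan says.** Two places in the protocol article set out what is to be learned. Strengths and Limitations states "We will observe the impact of the setting as compared with the content on acceptance" and names the means in the same sentence: "while asking for the preference for therapist-guided or self-management treatment". The objective in the abstract adds that the study will "collect information about preferences for on-site or at-home treatment".

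The structure of the trial is in the Design section: "The study design is a 2-arm proof-of-concept RCT", "There will be no crossover between conditions", and "we will use a 1:1 ratio randomization procedure". The intervention sections describe VR-CBT as manualised therapy given in a clinic under a psychotherapist. Calm Place is a commercial relaxation program that participants run themselves at home, without personalised or social-interactive parts. Strengths and Limitations confirms that "only the active treatment is culturally adapted and guided by a psychotherapist".

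Preference is measured before allocation, under Randomization and Masking: "They will report their preference for either treatment in a forced-choice question, rate their preference for each treatment on a scale from 1 to 10". The same sentence adds an open comment on the reason for the choice. The section on screening, consent and randomisation says that people who decline one of the treatments will be counted, as evidence on acceptance.

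**The concern.** A comparison of setting with content needs something that varies one while the other stays put. The article describes no arm, no structured item and no analysis that does this. Someone who picks VR-CBT may want the clinic, the therapist, the Inuit-specific material or the therapy itself, and the forced choice and ratings come out the same in each case.

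At stake is how acceptance and preference will be interpreted. Feasibility and acceptance are central to this trial, and Randomization and Masking says the preference data are meant to inform later trials and services. A majority for VR-CBT could be reported as a preference for on-site care when it reflects the therapist or the cultural adaptation. A majority for Calm Place could be reported as a preference for home when it reflects a wish for self-management.

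**Working it through.** The article gives no figure for this point, so there is none to reproduce. The question is whether separate effects can be identified.

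**Inputs.** Two arms, no crossover and 1:1 allocation (Design); 20 participants per arm (Sample Size); the description of each arm (the two intervention sections and Strengths and Limitations).

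| Component | VR-CBT | Calm Place |
|---|---|---|
| Place | clinic | home |
| Guidance | psychotherapist | self-managed, nonpersonalised program guidance |
| Cultural adaptation | yes | no |
| Therapeutic content | CBT focused on emotion regulation | guided relaxation and meditation |

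Biofeedback is left out of the table. It is described for VR-CBT, and its absence from Calm Place is implied but not stated. The argument does not need it.

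**Between-arm measures (attendance, attrition, use).** Code setting S = 1 for clinic and content C = 1 for adapted CBT, and write the expected outcome as b0 + bS·S + bC·C.

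- VR-CBT, 20 rows of (1, 1, 1): mean = b0 + bS + bC.
- Calm Place, 20 rows of (1, 0, 0): mean = b0.
- Difference = bS + bC.

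The S and C columns are identical, so their correlation is 1 and the matrix has rank 2 of 3. For a package difference D, the splits (D, 0), (0, D) and (D/2, D/2) fit equally well. Adding a guidance column gives rank 2 of 4. Separating cultural adaptation from therapeutic content would add one more identical column and leave the rank at 2. More participants repeat the same two rows, so sample size does not help.

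For contrast, an illustrative layout of 10 per cell that crosses setting with content has rank 3 of 3, and both main effects can be estimated.

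**Preference measures.** These are within-person, because each participant judges both options, but the options are still the two packages. If a participant's liking is the sum of parts, rating of VR-CBT minus rating of Calm Place = uS + uG + uC (setting, guidance, content). That is one equation in three unknowns. The forced choice gives only the sign of this sum. Refusals are counted per treatment and have the same limit.

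**Open comments.** These are the one described item in which a participant can name a part, for example being at home or having a therapist. They are reasons given for choosing one bundle over the other. They are not answers to a common question about each part, so they can illustrate motives but cannot give a structured comparison of setting with content.

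**The case against.** The strongest reply is that the article claims less than a separated effect. The verb is observe, the sentence sits in the Discussion, and no component effect appears among the aims, measures or analyses. The section on gaps in research says that counting people who accept only one treatment gives some indication of initial perceptions. The Conclusions openly pair therapist guidance with the clinic and self-management with the home. The abstract's objective is modest too: one option is on-site, the other is at home, and preferences are collected.

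Much of this stands. It makes the point one of over-claimed interpretation, not a faulty analysis. It does not rescue the sentence in Strengths and Limitations, which sets setting against content, and no described structured measure can do that.

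Four stronger readings are tempting and are not supported:

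- *Preference data say nothing about reasons.* This is too absolute. The open comments ask for reasons, and the feasibility section also collects reasons for dropping out where possible and diary comments.
- *The result would misdirect remote delivery.* The article mentions remote therapy as future work but does not tie the preference result to it.
- *No item separating the parts exists.* The questionnaire is not shown, and an article may summarise it. What can be said is that none is described.
- *The efficacy comparison is undermined.* A package comparison on the DERS-16 is legitimate and does not depend on this sentence.

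**Conclusion.** The point holds in a limited form. Setting, therapist guidance, cultural adaptation and therapeutic content are fully aliased with arm: rank 2 of 3 with setting and content, and 2 of 4 with guidance. Between-arm differences in acceptance, and the forced choice, ratings and refusals, therefore describe whole packages at any sample size. The comments add qualitative hints and no more. The stated comparison of setting with content cannot be made from the measures described, and the on-site or at-home objective is met only in the sense of a choice between two bundles.

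This rests on the arms being delivered as described and on the preference items being those listed under Randomization and Masking. Severity is modest: the DERS-16 comparison, randomisation and sample size are untouched, but the repair is cheap and lets the trial answer a question that it sets itself.

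**What to change.** 1. Reword the sentence in Strengths and Limitations to say that preference between two whole packages is observed, together with the reasons participants give, and that between-arm differences in acceptance are not attributed to setting or to content.
2. Add a few short items before randomisation, each varying one part:
   - clinic or home, for the same therapist-guided programme;
   - therapist-guided or self-guided, at the same place;
   - how important Inuit-specific content is to the participant.
3. Use the existing open comments as supporting evidence for these items.

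If the full questionnaire already holds such items, it is enough to cite them and reword the sentence.

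The cost is a few fields in REDCap, a sentence or two of wording and about a minute of participant time. The answers would be hypothetical preferences for options that participants have not tried, and should be reported as such. Arms, treatments and sample size stay as they are.

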### Conclusions

The proposed study responds to the community’s desire for accessible and appropriate resources for psychological well-being, as it was developed in active collaboration with the Inuit community in Québec. We will observe preference for therapist-guided, at-clinic treatment, or at-home self-management and compare the acceptance and feasibility of a culturally adapted, VR-assisted psychotherapy with a commercial self-management program in VR. We incorporate novel technology in providing treatment and in objective outcome measurement in the area of Indigenous health. We also aim to fulfill the needs for RCTs to test the efficacy of culturally adapted psychotherapies.

## Appendix

Multimedia Appendix 1 The appendix contains the treatment manual for psychotherapists (for use contact [name]).

## Abbreviations

AUC: area under the curve
AUDIT: Alcohol Use Disorders Identification Test
CBT: cognitive behavioral therapy
CORE: clinical outcomes in routine evaluation
DAST: Drug Abuse Screening Test
DERS: Difficulties in Emotion Regulation Scale
GAD-7: Generalized Anxiety Disorder 7-item
PC-PTSD-5: Primary Care Screen for Post-Traumatic Stress Disorder Diagnostic and Statistical Manual 5 version
PHQ-9: Patient Health Questionnaire 9-item
RCT: randomized controlled trial
REDCap: Research Electronic Data Capture
SDS-C: Severity of Dependence Scale for Cannabis
SPIRIT: Standard Protocol Items: Recommendations for Interventional Trials
VR: virtual reality
VR-CBT: virtual reality–assisted cognitive behavioral therapy
WEMWBS: Warwick-Edinburg Mental Well-Being Scale.
